### Participant timeline

Figure 2 shows the recommended SPIRIT figure with the participant timeline.

**Fig. 2 Fig2:**
[figure not shown]
Recommended SPIRIT figure with the participant timeline

### Sample size

The number of participants in this study considered the most recent meta-analysis study, which found a reduction of 5 mmHg caused by beetroot juice rich in nitrate in patients with SAH as significant with a variation of 4 mmHg [10, 11]. We applied these values in the Hedwig Harvard Sample Calculator software online, considering a bilateral 95% confidence interval and a power analysis of 80% that provided a minimum of 11 participants for this clinical trial [29]. We will recruit sixteen postmenopausal women diagnosed with SAH to ensure a sufficient sample size after the interventions. This sample size is consistent with previous studies that investigated the effects of BRJ on BP in patients with SAH. The Amaral et al. [29] study used 13 postmenopausal women to examine the impact of BRJ on PEH. Broxterman et al. conducted two studies in patients with SAH medicated and non-medicated. In both trials, the sample was 13 and 14, respectively. The most recent investigation in this field conducted by Siervo et al. [53] used 16 patients with SAH.

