**Methods:**

We will investigate the effects of beetroot juice rich in NO3 acutely (800 mg) and during a week with daily doses (400 mg) on blood pressure, heart rate (HR), cardiac autonomic control, endothelial function, inflammatory, hormonal, and stress biomarkers oxidative stress and enzymes involved in nitric oxide synthesis and mitochondrial regulation, under resting conditions, as well as mediated by submaximal aerobic exercise sessions. Through a randomized, crossover, triple-blind, placebo-controlled clinical trial, 25 physically inactive women with SAH will undergo an acute and 1-week trial, each with two intervention protocols: (1) placebo and (2) beetroot, in which will ingest beet juice with or without NO3 in its composition with a 7-day washout interval. On collection days, exercise will be performed on a treadmill for 40 min at a speed corresponding to 65–70% of VO2peak. The collection of variables (cardiovascular, autonomic, and blood samples for molecular analyses) of the study will take place at rest (135 min after ingestion of the intervention), during exercise (40 min), and in the effort recovery stage (during 60 min) based on previously validated protocols. The collections were arranged so that the measurement of one variable does not interfere with the other and that they have adequate intervals between them.

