Considering that the endogenous production of NO is reduced with aging [13], it was recently confirmed that the hypotensive effects caused by beetroot juice are more evident in older adults (50 to 70 years of age) when compared to a young population (18 to 30 years of age) [14]. In addition, a meta-analysis recently published by our group showed that in patients with SAH, NO3-rich beetroot juice supplementation was able to reduce systolic blood pressure by − 4.95 mmHg (95% CI: − 8.88; − 1.01) without significant differences to diastolic blood pressure [10].

Accordingly, physical exercise is considered one of the non-drug therapeutic strategies that directly helps to reduce blood pressure levels by causing post-exercise hypotension (PEH) [15] and contributing to increased baroreflex sensitivity [16]. HPE has excellent clinical value for hypertensive patients, as it can be used as a strategy to reduce blood pressure levels both acutely and chronically. Aerobic exercise is considered one of the most efficient to generate PEH [17–19].

In conjunction with heart rate (HR) and blood pressure (BP) levels, heart rate variability (HRV) has been used as a non-invasive and independent metric for assessing cardiovascular risk [11, 20, 21]. Through the adjacent intervals between consecutive heartbeats (RRi), it is possible to analyze the behavior of autonomic efferents (parasympathetic and sympathetic) on the heart [22, 23]. Part of the effects caused by hypertension on cardiac activity involves adjustments in the autonomic nervous system (ANS), and therefore, in hypertensive patients, there is a decrease in HRV at rest [24], and after exercise, there is a delay in recovery of parasympathetic modulation [25]. These two factors are evidence of autonomic dysfunction and cardiovascular inadaptability that certainly contribute to the emergence of disorders and adverse cardiovascular events [26] and a risk factor for overall mortality [27]. In SAH, endothelial dysfunction is documented in the macro- and microcirculation of the coronary, peripheral, and renal circulation. These effects are mainly caused by decreased endogenous nitric oxide production through increased oxidative stress and endothelial damage caused by increased blood shear force [28].

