### Trial design

The study is classified as a randomized, crossover, triple-blind, placebo-controlled clinical trial and will have two arms. The study protocol is registered on the ClinicalTrials.gov platform (NCT05384340) and described according to the Standard Protocol Items: Recommendations for Interventional Trials (SPIRIT) checklist. The results from this clinical trial will be described following the Consolidated Standards of Reporting Trials (CONSORT) guidelines.

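### The stated 80% power with a minimum of 11 women is unsupported: the 4 mmHg variation is undefined and appears to be the confidence-interval half-width of a pooled mean

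*Protocol article*

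**What the plan says.** The Sample size section bases the calculation on a meta-analytic fall of 5 mmHg, described as found "in patients with SAH as significant with a variation of 4 mmHg", and cites references 10 and 11 for it. These two values went into an online calculator with a two-sided 5% level and a power of 80%. The result is reported as "a power analysis of 80% that provided a minimum of 11 participants for this clinical trial". The section then sets the target: "We will recruit sixteen postmenopausal women diagnosed with SAH to ensure a sufficient sample size after the interventions". It supports this by noting that comparable studies enrolled 13 to 16 patients.

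The Background and rationale section gives the result of reference 10, where the juice is said to "reduce systolic blood pressure by − 4.95 mmHg (95% CI: − 8.88; − 1.01".

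The Trial design section reads: "The study is classified as a randomized, crossover, triple-blind, placebo-controlled clinical trial and will have two arms". Blood pressure is the primary outcome. The sequence-generation section works with 16 sets, but the abstract says "25 physically inactive women with SAH will undergo an acute and 1-week trial".

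No section gives an SD of systolic pressure, a within-woman SD, a within-woman correlation or an SD of paired differences.

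**The concern.** The two calculator inputs look like the pooled estimate and its CI half-width, each rounded to a whole number. A half-width shrinks as more or larger trials are pooled, so it says nothing about how much one woman's pressure varies from one period to the next. If it was entered where an SD belongs, the resulting sample size has no valid basis.

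What is at stake is how a null result would be read. The Discussion attributes an earlier null finding to a low nitrate dose. If this trial is also null at its higher dose, readers will lean on the stated 80% power to conclude that nitrate does not lower pressure by 5 mmHg. That conclusion is only as good as the variance behind it. The enrolments of other studies do not repair this, because they show precedent and not power.

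**Working it through.** **Inputs.** Difference 5 mmHg, variation 4 mmHg, two-sided 5%, power 80% (Sample size). Pooled mean −4.95, 95% CI −8.88 to −1.01 (Background). Two-treatment crossover (Trial design). N = 11 and 16 (Sample size), 25 (abstract).

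**1. Where the 4 appears to come from.** Half-width = (8.88 − 1.01)/2 = 3.935, which rounds to 4, just as 4.95 rounds to 5. The implied standard error of the pooled mean is 3.935/1.96 = 2.01. No other figure in the article could serve as a variability of about 4 mmHg.

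**2. Reproducing the stated 11.** The normal formula with 4 as a within-woman SD is

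n = 2 × (1.960 + 0.842)² × 4²/5² = 2 × 7.85 × 0.64 = 10.05, rounded up to **11**.

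The same expression gives 11 per arm if 4 is the common SD in a parallel comparison. Other uses of 4 do not give 11:

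- SD of the paired differences: 7.85 × 16/25 = 5.02, so 6 (8 by the t distribution).
- One-sided version of the formula above: 8.
- Within-woman SD, by t: 13.
- Parallel groups, by t: 12 per arm.

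So the 4 acted as a patient-level SD.

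**3. If 4 really were the within-woman SD.** The SD of differences would be 4 × √2 = 5.66. Power by noncentral t would be 74% at n=11, 91% at n=16 and 99% at n=25. Even on this reading, 11 women fall short of 80%.

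**4. What 80% power requires.** For one paired contrast in a balanced two-period crossover, the noncentrality is 5/(SD/√n) with n − 2 degrees of freedom, where SD is that of the within-woman differences. For example, n=16 and SD 8 give 5/(8/4) = 2.5 on 14 df, and 64% power. The largest SD that still gives 80% power is 5.3 (n=11), 6.6 (n=16) or 8.5 (n=25).

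**5. Power over a range.** The SDs below are assumptions, since the article gives none.

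| SD of differences (mmHg) | N for 80% | Power, n=11 | Power, n=16 | Power, n=25 |
|---|---|---|---|---|
| 6 | 14 | 69% | 87% | 98% |
| 8 | 23 | 46% | 64% | 85% |
| 10 | 34 | 32% | 46% | 67% |
| 12 | 48 | 24% | 34% | 51% |

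**6. Detectable difference at 80% power.** This scales with the SD, as 5 × SD/(largest SD for that n). At n=16: 5 × 8/6.64 = 6.0, 5 × 10/6.64 = 7.5 and 5 × 12/6.64 = 9.0 mmHg.

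**The case against.** Four objections deserve weight.

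- **The origin of the 4 is inferred.** The article never calls it a half-width, leaves variation undefined and also cites reference 11, which is not at hand. This stands, so the accurate wording is that the 4 appears to be the half-width. The defect does not depend on it: the figure is attributed to a meta-analysis, is not defined as any kind of SD, and does not give 80% power at 11 by t even as a within-woman SD.
- **Lack of power is not shown.** A reader might infer that the trial cannot detect 5 mmHg. The article does not support that, because it gives no true SD. With 16 women, power is 91% at an SD of differences of 5.66 and 87% at 6; with 25 it is still 85% at 8. Moreover, 11 is only the calculated minimum, and the plan recruits more.
- **The power model is simplified.** The trial measures pressure at rest and at 45 and 60 minutes after exercise, on days 1 and 7 of each period, and plans an adjusted mixed model. The percentages here assume a single paired contrast, so they indicate scale and do not forecast the power of the final analysis.
- **The source effect may seem wrong for an exercise trial.** A reader might infer that a general supplementation effect cannot inform this study. The objective also covers resting conditions, and resting pressure is measured, so that criticism is not made here.

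**Conclusion.** The stated 80% power is unsupported. The arithmetic from 5 and 4 to 11 is correct; the fault lies in the input. The 4 mmHg is undefined, matches the half-width of a pooled mean from the cited meta-analysis, and was used in the place of a patient-level SD. Whether true power lies above or below 80% cannot be settled from the article. It turns on whether the SD of the within-woman difference exceeds about 5.3, 6.6 or 8.5 mmHg for 11, 16 or 25 women. Over assumed SDs of 6 to 12 mmHg, power at the 16 planned in Sample size runs from 87% down to 34%, and at the abstract's 25 from 98% down to 51%. The unresolved choice between 16 and 25 therefore matters to the answer. These figures rest on a single paired systolic contrast, balanced sequences, no dropout and a true difference of 5 mmHg.

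**What to change.** Rewrite the Sample size paragraph:

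- Replace the 4 mmHg with an SD of the within-woman nitrate-minus-placebo difference in systolic pressure, and name its source. This could be one of the cited trials, if it is a crossover and reports such an SD, or the team's own repeat pressure readings.
- State the formula used and the blood pressure contrast to which it applies.
- Reconcile the 16 in Sample size and sequence generation with the 25 in the abstract.
- Restate power for 5 mmHg, or the detectable difference at 80% power, for the reconciled number. If power for 5 mmHg is below 80%, say so, so that a null result is read from its confidence interval.

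The cost is one paragraph and possibly a less favourable power statement. No extra enrolment is asked for; the Trial status section expected recruitment to end on January 31, 2023, so this corrects what is claimed and leaves conduct unchanged.

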### Recruitment

Recruitment will take place on a monthly basis. The dissemination of the study and recruitment will take place through media and communication channels. We will use local radio stations to publicize the study. In addition, we will post on social media (e.g., Facebook, Instagram) on research group pages and researchers’ personal profiles.

### Assignment of interventions: allocation

#### Sequence generation and implementation

We will use the randomizer.org website to randomize the order of intervention that participants will receive. For each treatment, 16 “sets” (total number of participants) will be created with two treatment options, “number 1” or “number 2.” Each number refers to a type of protocol and, therefore, will be previously coded by a researcher who will not participate in the experiments and the treatment allocation order will be respected (e.g., set 1—number 1; set 2—number 1; set 3—number 2; [...] set 16—number 1). After the end of the first intervention, the participants will perform the opposite intervention (Fig. 3).

**Fig. 3 Fig3:**
[figure not shown]
Study design flowchart

### Assignment of interventions: blinding

#### Who will be blinded

As this is a triple-blind study, clinical trial participants, researchers, and the outcome assessor will be blinded. Interventions will be codified by random letters or numbers, and a researcher not responsible for data collection will be responsible for keeping this complete information confidential. Only after data collection, processing, and analysis will the interventions be revealed. We do not anticipate any requirement for unblinding, but if required, the researchers will have access to group allocations and any unblinding will be reported.

### Data collection and management

#### Plans for assessment and collection of outcomes

Interventions and evaluations will be carried out at the Laboratory of Exercise Physiology and Metabolism at EEFERP. All assessments will be conducted by at least a physical educator, nutritionist, and nurse, trained and familiarized with the assessment protocol prior to the study.

#### Plans to promote participant retention and complete follow-up

The researchers will be in daily contact with the study participants. Your health status will be routinely asked, and survey requirements will be reinforced. Forty-eight and 24 h before assessments, text messages will be sent to remind participants of the assessment date and time. If any participant misses the assessment, we will immediately contact a call to inquire about the reasons for the no-show.

#### Data management

The information collected in this clinical trial will always be protected and in the care of the principal investigator. The data will be kept in your office and all investigation documents to ensure data security. Research information, when stored electronically, will have a copy stored on a drive that will be retained with a password for access and under the protection of the principal investigator ([name]).

### Statistical methods

For data analysis, descriptive statistics will be performed to characterize the sample. The results will be presented with mean and standard deviation values when the residual values of the variables present normal. Values in the median distribution and interquartile intervals will be presented when the residuals’ assumptions of normality and homoscedasticity are not reached. Data will be analyzed using linear analysis of mixed effects adjusted for age, drugs, and VO2peak, considering time and treatment as an independent variable. Per-protocol analysis will be performed to account for possible dropouts during the study. The analysis will be conducted according to the intention-to-treat principle. The generalized mixed linear model will treat the missing values, using maximum likelihood to estimate the model parameters. Differences in all tests will be considered significant when the *p* value is less than 0.05. The statistical program used will be RStudio (v. 1.0.136). The confidence interval at the 95% level will be exposed when we describe the comparison values of the variables with each other. The magnitude of significant differences will be quantified through effect size calculated using Cohen’s *d*. A large effect size will be considered for values greater than 0.9 and a medium effect size for values between 0.9 and 0.5 [54].

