
#### Exercise variables

On the first day, the collections will occur after the participants ingested 140 mL of beet juice (with or without nitrate). The seventh day of beet juice ingestion (70 mL) (with or without nitrate) will also be collected. On the collection days (first and seventh days of intervention), the variables will be obtained at the following times (Fig. 1):

I)Rest phase (zero to 135th min): After drinking the juice, the participants will remain at an initial rest in a sitting position. Then, 30 min before starting the measurements, the participants will be instructed to empty their bladders. Upon returning to the room, a recording strap (Polar® H10) will be placed on the chest, in the region of the distal third of the sternum, to record beat-to-beat HR throughout the collection, mediated by a heart rate monitor (Polar® RS800CX, Finland). Then, the participants will be placed on a stretcher in the supine position and will remain at rest. After the remaining time, HR values will be recorded (120th minute), HRV recording (120th to 125th min), systolic blood pressure (SBP) (125th minute), diastolic blood pressure (DBP) (125th minute), blood collection (15mL) (125th min), and analysis of endothelial function (flow-mediated dilation) (125th to 135th min).II)Physical exercise (135th to 175th min): Participants will perform the physical exercise for 40 min on a treadmill at a speed corresponding to 65–70% of VO2peak [29]. In this phase, the highest HR value reached during the exercise will be recorded, and the HRV recording will also be carried out in the last 5 min (35th–40th min).III)Recovery phase (175th to 235th min): At the end of the activity, the participants will be placed in the supine position again and will be monitored for another 60 min, recording their HR at 30 s, 60 s, 120 s, 180 s, and 300 s. Blood collection (15 mL) will be performed between 5 and 10 min after exercise. HRV will be recorded after exercise at the following times: 0–5 min, 10–15 min, 20–25 min, 30–35 min, and 40–45 min. SBP and DBP will be recorded after exercise at the 45th minute and 60th minute post-exercise. To avoid errors in the measurements of the evaluated parameters, a single evaluator will perform these measurements throughout the experiment. The flow-mediated dilation technique to assess endothelial function will be employed after exercise during the 50th–60th minute post-exercise interval.

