#### Linear indices

The time-domain analysis will be performed using the standard deviation of the mean of normal R-R intervals (SDNN) and square root of the mean of the square of differences between adjacent normal R-R intervals (RMSSD) indices. For the analysis of linear indices in frequency and time domains, the program Kubios HRV 2.1 analysis® will be used [45]. High-frequency spectral components (HF: 0.15–0.40 Hz) in absolute units (ms^2^) will be used to analyze HRV in the frequency domain. We will choose not to evaluate the low-frequency index (LF: 0.04–0.15 Hz) and the LF/HF ratio since the scientific literature demonstrates that its concept is defective and lacks empirical support to characterize vagal balance—sympathetic [46]. The spectral analysis will be calculated using the fast Fourier transform.

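### Failed residual checks change only the descriptive summary; for RMSSD, SDNN and HF power, an untransformed mixed model with one residual variance would misstate the error of treatment contrasts at single recovery windows

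*Protocol article*

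**What the plan says.** All points are from the Protocol article.

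- **Residual checks (Statistical methods).** Mean and SD are shown when residuals look normal. Otherwise "Values in the median distribution and interquartile intervals will be presented when the residuals’ assumptions of normality and homoscedasticity are not reached". No other consequence is stated.
- **Model (Statistical methods).** "Data will be analyzed using linear analysis of mixed effects adjusted for age, drugs, and VO2peak, considering time and treatment as an independent variable". This covers the data without exception. No transformation, variance function or non-Gaussian family is named.
- **Second model name (Statistical methods).** "The generalized mixed linear model will treat the missing values, using maximum likelihood to estimate the model parameters". No family or link is given, and the sentence concerns missing values.
- **Significance (Statistical methods).** "Differences in all tests will be considered significant when the *p* value is less than 0.05".
- **HF scale (Linear indices).** "High-frequency spectral components (HF: 0.15–0.40 Hz) in absolute units (ms^2^) will be used to analyze HRV in the frequency domain".
- **Time points (Exercise variables).** HRV is recorded at rest, in the last 5 min of exercise, and then: "HRV will be recorded after exercise at the following times: 0–5 min, 10–15 min, 20–25 min, 30–35 min, and 40–45 min". That makes seven windows per collection day. Blood is drawn twice per collection day.

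**The concern.** A residual check is there to decide whether the fitted model can be trusted. Here it decides only which summary goes in a table. A median printed beside a p value does not repair the standard error behind that p value.

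RMSSD, SDNN and HF power cannot fall below zero. When their level drops in exercise, their SD normally drops too. A model with one residual variance averages over all windows, so it gives too large an error where the level is low (exercise, early recovery) and too small an error where it is high (rest).

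The hypothesis concerns the response to and recovery from exercise, and the section on ultra-short-term analysis targets parasympathetic reactivation in the first 5 min. The Discussion attributes earlier null findings on HRV recovery to a low nitrate dose. A null result produced by the error term would look like one more failure of nitrate, now at the higher dose.

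**Working it through.** **1. The plan's own figure.** The Sample size section uses a study that "found a reduction of 5 mmHg caused by beetroot juice rich in nitrate in patients with SAH as significant with a variation of 4 mmHg", "considering a bilateral 95% confidence interval and a power analysis of 80% that provided a minimum of 11 participants for this clinical trial". Then 2 × (4 × (1.960 + 0.842) / 5)² = 10.05, rounded up to 11. The figure reproduces, but it concerns blood pressure only. The protocol gives no mean, SD or target effect for any HRV index, so every HRV input below is an assumption.

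**2. Set-up.** 16 women (Sample size section), two treatments, seven windows, log-normal data, nitrate multiplying every window by one ratio, two-sided 5% tests. In this balanced layout, the treatment contrast at one window has standard error √(2 × MSE / n). For a random-intercept model, MSE has (16 − 1) × 13 = 195 degrees of freedom.

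| Setting | Assumed level: rest; exercise; five recovery windows | Log-SD between / within women | True ratio |
|---|---|---|---|
| A, RMSSD (ms) | 25; 4; 6, 10, 14, 17, 20 | 0.4 / 0.25 | 1.25 |
| A, HF (ms²) | 200; 5; 10, 30, 70, 110, 150 | 0.8 / 0.5 | 1.5 |
| B, RMSSD (ms) | 25; 4; 6, 9, 13, 16, 18 | 0.5 / 0.3 | 1.3 |
| B, HF (ms²) | 200; 3; 10, 30, 60, 90, 120 | 1.0 / 0.6 | 1.7 |

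**3. Log-scale power by hand.** The standard error is SD × √(2/16), and power is Φ(ln ratio / SE − 1.96).
- A, RMSSD: 0.2231 / 0.0884 = 2.525; power 71%.
- A, HF: 0.4055 / 0.1768 = 2.294; power 63%.
- B, RMSSD: 0.2624 / 0.1061 = 2.474; power 70% (simulated 69%).

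**4. The mechanism by hand (setting B, model with a subject-by-time effect).** If SD is proportional to level, the pooled SD is proportional to the root mean square of the levels.
- RMSSD: squares sum to 1507; √(1507/7) = 14.67. At rest the standard error is 14.67/25 = 0.587 of its proper size, so type I error is 2 × (1 − Φ(1.96 × 0.587)) = 25% (simulated 25%). At 0–5 min it is 14.67/6 = 2.45 times too large, so type I error is about 0.
- HF: squares sum to 67,109; √(67,109/7) = 97.9. At rest the factor is 97.9/200 = 0.490, which gives 34% (simulated 34%).

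With a random intercept only, multiplicative differences between women also enter the pooled error. That lowers the resting inflation and costs further power in early recovery.

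**5. Simulated window contrasts, random intercept only.**

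| | Raw power over the five recovery windows | Log power, each window | Resting type I error, raw / log |
|---|---|---|---|
| A, RMSSD | 0, 9, 36, 54, 66% | about 71% | 14% / 5% |
| A, HF | 0, 0, 4, 24, 45% | about 63% | 17% / 5% |
| B, RMSSD | 0, 5, 29, 48, 56% | about 69% | 16% / 5% |
| B, HF | 0, 0, 4, 18, 35% | about 70% | 23% / 5% |

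**6. Sensitivity.**
- RMSSD, between-woman log-SD 0.2–0.8 and within-woman 0.2–0.5: resting error is 4–24% with a random intercept only, and at least 12% in nine of the twelve combinations. The 4% occurs at 0.8 / 0.2. With a subject-by-time effect it is 24–25% throughout.
- In that grid, 0–5 min power for a ratio of 1.4 is 0–23% raw against 47–100% log.
- If RMSSD falls only from 25 to 10 ms, resting error is 11.7% and 0–5 min power is 18% against 71%.
- With 25 women (the number in the Abstract), 0–5 min power in setting A stays at 0.3% (RMSSD) and 0% (HF).

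**7. Other analyses the text would allow.**
- Overall treatment effect, raw, setting A: type I error 2.0% (RMSSD) and 1.1% (HF); power 99.7% and 81%, against about 100% on the log scale. The treatment-by-time test has type I error 1.9% and 1.6%.
- Separate raw paired tests per window: type I error 3–5%. HF power in setting A is 35% against 57% on the log scale (22 points lost), and in setting B 32% against 65%. Across variants of setting A, HF loses 16–23 points and RMSSD 3–9.
- A skewed blood marker with similar means at the two draws (2 and 2.3): type I error 3–6%; power 34–46% raw against about 65% log.

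**The case against.** The strongest objection is that the criticised model is partly inferred. The text does not state a raw scale, one model over all seven windows, a common residual variance or contrasts by window. The sentence about medians governs presentation, and absolute units may name only the measurement unit of HF. An article may leave such details to a full protocol or analysis plan that is not shown.

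Part of this stands: the size of the effect depends on those choices. It does not dispose of the point. The section does state a rule for failed checks, that rule stops at the summary statistics, and the model it names is linear. The one mention of a generalized model is tied to missing values and settles nothing.

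A reader might infer three stronger claims that are not supported:
- **That recovery effects are nearly untestable.** Near-zero power is confined to about the first 15 min for RMSSD and 25 min for HF. Early vagal recovery is also measured by heart rate recovery at 30 to 180 s, which this does not touch.
- **That resting tests are anti-conservative in general.** This needs a pooled variance and contrasts at single windows. The overall tests are conservative, and paired tests per window keep their size.
- **That the same error inflation reaches the blood markers.** With similar means at both draws they lose power only.

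**Conclusion.** The point holds for window-specific treatment contrasts on RMSSD, SDNN and HF power. If they are analysed untransformed with one residual variance, power at 0–5 min of recovery is about 0% against 63–71% on the log scale. By 40–45 min the gap is 45–67% against 61–72% in setting A, and wider for HF in setting B (35% against 70%). Resting type I error is typically 12–25%, 4% in one corner of the RMSSD grid, and up to 34% for HF. SDNN was not simulated; it is included because it is positive and recorded in the same windows.

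These sizes rest on assumed levels, SDs and ratios, on log-normal data and on model defaults that the text does not spell out. The direction follows from SD changing with level. Only secondary outcomes are affected, and the primary outcome, blood pressure, is little touched. The change should be made, but the primary conclusion does not depend on it.

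**What to change.** In Statistical methods, turn the rule on residual checks into an analysis rule:

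- RMSSD, SDNN, HF power and right-skewed blood markers are natural-log transformed before the mixed model. Treatment effects are back-transformed and reported as nitrate/placebo ratios of geometric means with 95% confidence intervals.
- Where residual checks still show unequal variance, residual variance may differ by time point (for example a variance function by time in the R package nlme).
- Median and interquartile range remain as descriptive summaries only.
- Blood pressure, heart rate and heart rate recovery stay on their own scale.

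The cost is one or two sentences and a few lines of code, with no new data and no more participants. Effects on these outcomes will read as ratios, and a few extra variance parameters may be needed. Settling this before unblinding also prevents a choice of scale guided by the results.
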